### Sample size and power calculations

To effectively test the presence of a relationship between pre-treatment imaging markers and post-treatment symptomatic response the study sample size will need to be large enough to overcome the neuroimaging problem of multiple comparisons across the ~300,000 intra-cerebral image voxels and also account for participant attrition. The attrition rate observed during a similar trial (i.e., Adolescent Depression Antidepressants and Psychotherapy Trial [ADAPT]) with a 28-week follow-up period was just 2% [43]. Allowing for an even greater attrition rate of 20% on a pre-treatment sample size of 40 patients per treatment arm, it follows that 32 patients will be available for post-treatment scans. Assuming an effect size of the same size as that observed in a previous study of adults with MDD (R ≥ 0.76 for grey matter volume [GMV] and symptom response in ACC) [8] and a conservative two-tailed probability of p <0.001 to control for multiple comparisons in a whole brain analysis of imaging data, and at least 32 patients completing post-treatment scans, the power to detect a true effect will be at least 95%. Thus with pre-treatment imaging data from 40 patients per treatment arm, the study is strongly powered to assess imaging predictors of recovery following treatment for MDD.

To detect CBT-related changes in brain function, a previous fMRI study of adult MDD [9] and a pilot study examining components of variance in a facial emotion perception task [44] are used to inform calculations of statistical power. Activation of the left amygdala by facial emotion processing showed an effect of antidepressant treatment of d = 1.02 [9]. A similar effect size of CBT will be assumed for the current study, with empirical estimates of between-subject and between-session variance in amygdala response [44] suggesting that a minimum power of 80% will be needed for detection of a true treatment effect. Considered together with a false positive rate of 5%, a minimum of 30 participants will be needed for the detection of CBT-related changes in brain function. The effects obtained in 40 patients in the CBT arm, compared to 40 healthy adolescents, should therefore be sufficiently powerful in size to detect therapeutic changes in amygdala activation equivalent to that observed from antidepressant medication treatment studies of adult patients with MDD.

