### Follow-up assessment

Patients who were randomized to the CBT arm of the IMPACT clinical trial who have completed a minimum of 6 out of a maximum of 20 offered CBT therapy sessions will be invited back for a second MRI visit approximately 24 weeks following their first therapy appointment. All healthy comparison participants will be invited back for a second MRI visit at least 24 weeks from their first scan date to ensure a comparable length of time has passed between scans across groups. Due to financial constraints, no sMRI and DTI sequences will be performed at the second MRI visit. All participants will complete the same fMRI tasks collected during the first MRI visit (e.g., implicit facial expression recognition, emotional go/no go, encoding and retrieval, and resting state tasks). In line with procedures undertaken at the first scan, STAI measures will be obtained prior to scanning whereas SMFQ and Bond VAS measures will be obtained after the scan.

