#### *sMRI data analysis plan*

Whole brain, multi-channel segmentation [45] and voxel-based morphometry [46] will be used to generate GMV maps from each baseline scan for co-registration into Montreal Neurological Institute (MNI) standard space [47]. Whole brain voxel-based morphometry will first be used to assess the presence of pre-treatment anatomical differences between patients and controls and to explore regions where variation in grey or white matter significantly predict treatment-specific or treatment-general responses [8]. The multivariate technique of partial least squares [48] will also be used to identify patterns of grey matter variation that optimally correlate with treatment response. In an effort to test our hypotheses comprehensively, we will also use the MNI template [49] to anatomically parcellate a priori regions of interest including, but not limited to, subgenual, pregenual and dorsal ACC, amygdala, hippocampus, and prefrontal cortex, where the presence of both group differences in GMV and associations with treatment-specific symptom reductions will be assessed. Non-parametric statistical methods with correction for multiple comparisons [50-52] will be used.

With regard to the DTI dataset, fractional anisotropy and mean diffusivity maps will be created using the Functional Magnetic Resonance Imaging of the Brain (FMRIB) diffusion toolbox in FMRIB Software Library (FSL) [53] by estimating diffusion tensors at each intracerebral voxel prior to using a b = 0 image for mapping into MNI standard space. As with the sMRI data, between-group differences and predictors of treatment response in fractional anisotropy and diffusivity measures will be identified across the whole brain and in a priori regions of interest. For further exploration of group differences and associations with treatment outcome, anatomical connections between frontal and limbic cortex will be measured using probabilistic tractography [54-56].

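### The 'at least 95%' power for the whole-brain predictor analysis is computed at p<0.001, which does not correct for about 300,000 voxels, so it is not the power of the planned corrected test

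*Protocol article*

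**What the plan says.** In the protocol article, 'Sample size and power calculations' sets the task as finding imaging predictors of response despite "multiple comparisons across the ~300,000 intra-cerebral image voxels". Its inputs are:

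- 40 patients per arm with 20% attrition, from which "it follows that 32 patients will be available for post-treatment scans";
- an effect taken from a previous adult study, "R ≥ 0.76 for grey matter volume [GMV] and symptom response in ACC";
- a significance level described as "a conservative two-tailed probability of p <0.001 to control for multiple comparisons in a whole brain analysis of imaging data".

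From these it states that "the power to detect a true effect will be at least 95" per cent, and concludes that the study has strong power for predictors of recovery.

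'sMRI data analysis plan' covers whole-brain voxel-based morphometry and a priori regions that include three parts of the ACC. Inference is by "Non-parametric statistical methods with correction for multiple comparisons". 'fMRI data analysis plan' follows the same approach. Neither section gives a numerical corrected threshold, names the error rate (familywise or false discovery), or says whether inference is voxelwise or clusterwise.

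'Follow-up assessment' restricts the second scan to "Patients who were randomized to the CBT arm of the IMPACT clinical trial" who attended at least 6 sessions, plus the healthy controls. It also says that structural and diffusion sequences are not repeated.

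**The concern.** The power paragraph names the multiplicity problem and then treats p<0.001 as the answer to it. At that level a whole-brain map of 300,000 voxels is close to uncorrected. The analysis sections promise corrected inference, so the power quoted belongs to a more lenient test than the one planned.

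Prediction of response to each of the three treatments is a stated aim. A reader who accepts the power claim could take an empty corrected whole-brain map as good evidence that no predictor exists, although the map may have had a substantial chance of missing even a correlation of 0.76.

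The justification of the 32 has a separate problem. It counts post-treatment scans in every arm, but two of the three patient arms are never rescanned, and nobody has a second structural scan. The powered effect relates baseline grey matter volume to symptom response. It needs a baseline scan and a later symptom measure, not a second scan.

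**Working it through.** **Inputs from the sample size section.** r = 0.76 (the lower bound of the stated range), 40 × 0.8 = 32 patients per arm, two-sided alpha 0.001, about 300,000 voxels. The effective number of independent tests is not given. The values 500 to 10,000 below are assumptions, used to show a range.

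**Formula.** For one correlation tested against zero, Fisher z gives power = Φ(atanh(r)·√(n−3) − z), where z is the normal quantile at 1 − alpha/2. As a check, power was also computed from the exact critical r of the t test and by simulating bivariate normal samples.

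**1. The article's own figure.** atanh(0.76) = 0.996, and 0.996 × √29 = 5.37. With z = 3.29, Φ(5.37 − 3.29) = 98.1%. Simulation also gives 98.1%. The statement of at least 95% is therefore correct for a single test.

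**2. What p<0.001 controls.** 0.05 / 50 = 0.001, so it is a Bonferroni level for 50 tests. Over the stated voxels, 300,000 × 0.001 = 300 are expected to pass on a null map.

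**3. Full Bonferroni.** 0.05 / 300,000 = 1.67 × 10⁻⁷, with z = 5.23. Fisher z power is Φ(5.37 − 5.23) = 55%. The critical |r| at 30 degrees of freedom is 0.777, above the assumed effect of 0.76. Simulation accordingly gives power just below one half, 43.5%.

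**4. Scenarios at n = 32, r = 0.76, voxelwise familywise 0.05.**

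| Effective tests | Alpha per test | Power: exact critical r | Power: Fisher z |
|---|---|---|---|
| 300,000 | 1.67 × 10⁻⁷ | 44% | 55% |
| 10,000 (assumed) | 5 × 10⁻⁶ | 74% | 79% |
| 1,000 (assumed) | 5 × 10⁻⁵ | 89% | 90% |
| 500 (assumed) | 1 × 10⁻⁴ | 92% | 93% |
| 250 (assumed) | 2 × 10⁻⁴ | 94.5% | 95.0% |
| 200 (assumed) | 2.5 × 10⁻⁴ | 95.2% | 95.6% |
| 12 (regional set, assumed) | 4.17 × 10⁻³ | 99% | 99% |

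Power reaches 95% only at about 200–250 effective tests or fewer.

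**5. If all 40 patients per arm have outcomes.** Full Bonferroni gives 73–80%, and 500 effective tests give about 98%.

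**6. The event behind n = 32.** The sample size section relies on "at least 32 patients completing post-treatment scans" in each arm. 'Follow-up assessment' offers rescans only to CBT patients and omits structural imaging. The two cannot both describe the predictor analysis. Counting patients with a baseline scan and a symptom outcome at the same 20% loss leaves 32 unchanged.

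**The case against.** The strongest reply is that the plan never commits to Bonferroni. Image smoothness makes voxels dependent, and permutation methods with clusterwise or false discovery rate correction could give quite different power. This stands. A reader might infer that power at the plan's own corrected threshold is 44–92%. The documents do not support that, because they state no such threshold. The low end assumes full Bonferroni and the high end assumes 500 effective tests.

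A reader might also infer that positive findings would be unprotected against chance. That does not follow either. No section declares results at uncorrected p<0.001, and the analysis sections promise correction. The 300 null voxels show what the threshold fails to control, not what will be reported.

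Third, the a priori ACC regions are where the assumed effect was seen, and a small corrected set of such tests keeps about 99% power at r = 0.76. So the documents do not show that the study is underpowered throughout. But this does not rescue the sentence, which claims power for a whole-brain analysis. The article's own section on the limitations of earlier studies argues for samples large enough for whole-brain work.

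Fourth, 32 is a cautious count: 20% attrition is allowed against 2% in a similar earlier trial. This is fair, and the number does not change; only its description is wrong.

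Finally, the adult ACC correlation is openly labelled an assumption. Asking for power at smaller correlations would be a preference, since the documents offer no other value.

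**Conclusion.** The concern holds as a fault in the power statement. The 95% is arithmetically correct for one test at p<0.001 (98% recomputed), but that level does not control for the 300,000 comparisons the same paragraph names, and it is not the corrected test that the analysis sections plan.

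The size of the gap cannot be fixed from the documents. Under voxelwise familywise correction with r = 0.76 and n = 32, it runs from about 44–55% power (Bonferroni over all voxels) to 92–93% (500 effective tests assumed). The claimed 95% is met only at about 200–250 effective tests or fewer. With 40 analysed patients the two scenarios give 73–80% and about 98%. Clusterwise or false discovery rate inference would give other values.

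The planned Type I error control is not in question, and the a priori regional tests remain well powered at the assumed effect. The post-treatment-scan basis for the 32 contradicts the follow-up section, but correcting it leaves the count unchanged.

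**What to change.** Rewrite the first paragraph of 'Sample size and power calculations':

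- Drop the word 'conservative' and the claim that p<0.001 controls for multiple comparisons.
- Say that power of at least 95% holds for a single test at two-sided p<0.001 with r = 0.76 and n = 32, or for a small corrected set of a priori region tests.
- State the corrected threshold (error rate, and voxel or cluster level) that the whole-brain analysis will use, and give whole-brain power at that threshold.
- Limit the conclusion about strong power to the analyses for which it is shown.
- Describe the 32 as patients per arm with a baseline scan and a post-treatment symptom outcome, to agree with 'Follow-up assessment'.

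The cost is one reworded paragraph and a less favourable stated power for the whole-brain search. No extra patients are needed, and the planned analyses do not change.

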#### *sMRI data analysis plan*

Whole brain, multi-channel segmentation [45] and voxel-based morphometry [46] will be used to generate GMV maps from each baseline scan for co-registration into Montreal Neurological Institute (MNI) standard space [47]. Whole brain voxel-based morphometry will first be used to assess the presence of pre-treatment anatomical differences between patients and controls and to explore regions where variation in grey or white matter significantly predict treatment-specific or treatment-general responses [8]. The multivariate technique of partial least squares [48] will also be used to identify patterns of grey matter variation that optimally correlate with treatment response. In an effort to test our hypotheses comprehensively, we will also use the MNI template [49] to anatomically parcellate a priori regions of interest including, but not limited to, subgenual, pregenual and dorsal ACC, amygdala, hippocampus, and prefrontal cortex, where the presence of both group differences in GMV and associations with treatment-specific symptom reductions will be assessed. Non-parametric statistical methods with correction for multiple comparisons [50-52] will be used.

With regard to the DTI dataset, fractional anisotropy and mean diffusivity maps will be created using the Functional Magnetic Resonance Imaging of the Brain (FMRIB) diffusion toolbox in FMRIB Software Library (FSL) [53] by estimating diffusion tensors at each intracerebral voxel prior to using a b = 0 image for mapping into MNI standard space. As with the sMRI data, between-group differences and predictors of treatment response in fractional anisotropy and diffusivity measures will be identified across the whole brain and in a priori regions of interest. For further exploration of group differences and associations with treatment outcome, anatomical connections between frontal and limbic cortex will be measured using probabilistic tractography [54-56].

#### *fMRI data analysis plan*

Standard preprocessing methods for all datasets will include correction for head movement [52] and appropriate control for potential confounds to BOLD signal dynamics such as fluctuation in cardiorespiratory rhythms [57]. A general linear model will be used to convolve the hemodynamic response function with fMRI-related contrasts of interest to provide estimates of BOLD signal on a voxel-by-voxel basis in MNI standard space. Hypotheses will be tested using the same approach as that undertaken in the sMRI data analyses, where between-group differences and predictors of treatment response in pretreatment BOLD signal will be identified across the whole brain and in a priori regions of interest. CBT-related changes in functional activation will also be examined. Univariate analyses will be followed-up by the multivariate approach of partial least squares to identify task-related patterns of functional activation relating to therapeutic outcome.

Resting state fMRI data will be analysed in a similar fashion to the functional task data. The Hurst exponent will first be estimated at each voxel in the resting state data. The Hurst exponent measures the randomness of a data set and as such, has been shown to be sensitive to the effects of disease and drug treatment [58,59]. Between-group differences and predictors of treatment response in pretreatment BOLD signal will first be identified across the whole brain and then in a priori regions of interest. CBT-related changes in the Hurst exponent will also be examined.

We will also measure functional connectivity between regions within the fronto-limbic system and construct graphical models that summarise the topological properties of fronto-limbic and whole brain networks [60,61] in the resting state data. Similar network analysis methods may then be applied to the DTI data set, thereby permitting an integrated functional and structural analysis of network abnormalities in depression. Nonparametric statistical methods of inference will again be applied to statistically evaluate fractal and network parameters [50-52,62].

#### *Longitudinal data analysis plan*

For the fMRI datasets collected at baseline and 24 weeks, we will fit a balanced, mixed effects 2 × 2 (group × time) analysis of variance (ANOVA) model to the brain activation data acquired on patients treated with CBT and healthy adolescents. A significant group × time interaction will identify the effect of CBT, for which appropriate post-hoc tests will be performed. Nonparametric statistical methods of inference correcting for multiple comparisons will be applied to statistically evaluate the main effects of group and time point, and any group × time interaction [50-52].

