### Study participants

The patient population will be recruited from a larger cohort of young people with depression who have agreed to take part in the IMPACT trial. All eligible and interested patients residing in London or Cambridgeshire will be invited to take part in MR-IMPACT, with enrolment targeted to reach 120 adolescents (male and female) aged 11 through 17 years who meet Diagnostic and Statistical Manual of Mental Disorders (DSM-IV) criteria for moderate to severe unipolar depression. Patients with chronic or recurrent MDD are also included, as are patients already taking antidepressant medication. A detailed list of the study exclusion criteria is provided below.

All patients will be provided an MR-IMPACT study information leaflet and will provide verbal consent to IMPACT research assistants to be contacted by telephone by an MR-IMPACT researcher a minimum of 48 hours later for potential participation in the MR-IMPACT study. Patients will be contacted to assess interest in and eligibility for the magnetic resonance imaging (MRI) scan. Patients with MRI contraindication will be ineligible and therefore excluded from the study at this point. For eligible patients, if the patient so chooses, one adult (typically a parent) may accompany the adolescent patient into the scanner suite. For the patients requesting this option, the identified adult will be screened over the telephone for MRI contraindications. Eligible patients will be scheduled for an MRI appointment where they are remunerated £30 for their time and inconvenience. Any fees incurred for travel to and from the MRI appointment will be reimbursed to the adult accompanying the patient.

A group of healthy control young persons matched for age, sex, intelligence quotient (IQ) and handedness will be recruited into the study for comparison. A letter will first be posted to all families with healthy adolescents who had participated in a previous study (i.e. the ROOTS study) [32]. The letter will describe the MR-IMPACT study and the current recruitment of siblings of ROOTS participants aged between 11 and 17 years, and request that interested families contact a member of the MR-IMPACT team to discuss participation and arrange a home visit. If needed, additional healthy control adolescents will be recruited from local schools within Cambridgeshire.

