### Inclusion criteria

1. Aged 11 through 17 years.

2. Current DSM-IV unipolar MDD diagnoses with moderate to severe impairment determined by child and parent interviews using the K-SADS-PL.

3. Score of 27 or more on the MFQ.

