## Discussion

An important challenge to adolescent mental health services is the provision of appropriate and effective treatment to adolescents in need at the earliest possible point in time. To overcome this challenge, accuracy in both diagnostic assessment and prognostic evaluation of patients are critical, but as yet clinicians possess no objective tools for either. Diagnostic assessments rely on subjective retrospective information transmission from patient and/or parent to clinician whereas potential prognostic indicators of treatment outcome, such as depressive symptom severity or suicidal tendencies, are poor [43]. Therefore the overall aim of MR-IMPACT is to identify and evaluate objective neurobiological markers of depressive illness in adolescence and prognostic indicators of recovery following psychological treatment for depression.

Neural markers of depression in adolescence will be characterized by comparing structural and functional differences in patients with MDD prior to treatment against a group of healthy adolescent participants matched for demographic characteristics such as age, sex and IQ. Treatment-related changes will be identified by measuring changes in brain functional activation and connectivity prior to treatment and following at least six attended sessions of CBT. A placebo-controlled trial would have been an optimal method for assessing treatment-related changes, but impossible due to ethical constraints. Therefore, changes in brain function in healthy adolescents will also be measured at a second time point matched in length to that of the depressed group to ensure that functional changes indicative of adolescent development are not misidentified as changes related to CBT treatment.

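### Attendance and attrition after recruitment can undo the control matching, and the stated group × time ANOVA has no age term to protect its reading as the effect of CBT

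*Protocol article*

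**What the plan says.** Under Study participants, the article states: "A group of healthy control young persons matched for age, sex, intelligence quotient (IQ) and handedness will be recruited into the study for comparison". It does not say whether matching is by pair or by frequency, or to which patients. Inclusion criteria set the patient age range: "Aged 11 through 17 years".

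Under Follow-up assessment, the second scan is offered to patients in the CBT arm "who have completed a minimum of 6 out of a maximum of 20 offered CBT therapy sessions will be invited back for a second MRI". On the other side, "All healthy comparison participants will be invited back for a second MRI visit". The session rule has no counterpart in controls.

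Sample size and power calculations allows 20% attrition on 40 patients per arm, leaving 32, and plans 40 CBT patients against 40 healthy adolescents.

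The Longitudinal data analysis plan then says "we will fit a balanced, mixed effects 2 × 2 (group × time) analysis of variance (ANOVA) model to the brain activation data acquired on patients"; these are the CBT patients, and the other group is the healthy controls. If the interaction is significant, it is taken to show the effect of CBT. The Discussion explains that controls are rescanned after an interval of matched length, "to ensure that functional changes indicative of adolescent development are not misidentified as changes related to CBT treatment".

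**The concern.** The patient and control groups are not randomised against each other. Their comparability rests on matching at recruitment and on a second control scan. The change analysis uses neither group as recruited: the patient side passes through an attendance rule and then through return for scanning, and the control side only through return. If attendance or return is related to age, sex or IQ, the rescanned groups can differ on the factors that were matched.

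A stable difference in level cancels within person in a group × time test. A difference in the rate of change does not. Ages run from 11 through 17, so developmental change over about 24 weeks may vary with age. In that case an age gap between the rescanned groups would appear in the interaction and be read as CBT, which is the error the controls are there to prevent. The stated model has no term that would detect or remove it.

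**Working it through.** **1. The article's own figures.** Attrition: 40 × (1 − 0.20) = 32, as stated. For CBT-related change it uses d = 1.02, 80% power and 5% alpha. With a two-sided normal approximation, n per group = 2 × ((1.960 + 0.842)/1.02)² = 15.1. That is 30.2 in total, or 32 after rounding up per group, so the stated minimum of 30 fits a two-group total. The variance components behind it are not given, so the exact route cannot be confirmed.

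**2. Is power the problem?** No. At d = 1.02, power is 99.5% for 40 v 40, 99.0% for 32 v 40 and 97.7% for 24 v 40. Unequal numbers alone cost almost nothing. The question is bias.

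**3. Bias from lost age matching.** All inputs here are assumptions, because the article gives no data on them:
- D: difference in mean age between CBT patients lost and those retained, 0 to 2 years.
- b: variation of 24-week change with age, 0.05 to 0.2 SD of change per year.
- Loss: 20% (the article's allowance) or 40% (assumed, because the six-session rule is a further route out of the analysis).
- All 40 controls return, and the groups were matched on age before loss.

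Formulas: age shift = loss × D; bias = b × shift; SE = √(1/n₁ + 1/40) in SD of change; type I error = Φ(−1.96 + bias/SE) + Φ(−1.96 − bias/SE), for one two-sided 5% test.

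| Loss | n₁ | D (years) | b | Shift (years) | Bias (SD) | Type I error |
|---|---|---|---|---|---|---|
| 20% | 32 | 0 | any | 0 | 0 | 5.0% |
| 20% | 32 | 1 | 0.1 | 0.2 | 0.02 | 5.1% |
| 20% | 32 | 2 | 0.2 | 0.4 | 0.08 | 6.3% |
| 40% | 24 | 1 | 0.1 | 0.4 | 0.04 | 5.3% |
| 40% | 24 | 2 | 0.2 | 0.8 | 0.16 | 9.5% |

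For the third row, SE = √(1/32 + 1/40) = 0.237 and bias/SE = 0.34, so type I error = Φ(−1.62) + Φ(−2.30) = 0.063.

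If d = 1.02 is on the same scale, the largest biases are 0.08/1.02 = 8% and 0.16/1.02 = 16% of the planned effect.

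**4. Chance imbalance, kept apart.** If ages are uniform over seven years, the SD is 7/√12 = 2.02 years. With random loss, the mean age of the 32 retained differs from that of their 40 with SE 2.02 × √(1/32 − 1/40) = 0.16 years. Against all 120 patients the SE is 2.02 × √(1/32 − 1/120) = 0.31 years, or about ±0.6 years at 95%. This is sampling variation that the test's error term already reflects, so it is not bias.

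**The case against.** The strongest reply is that the model is called unadjusted only because a condensed article does not mention covariates, which may stand in a fuller plan. That has force: the article does not exclude covariates, and silence alone would not be a finding. But this article does more than stay silent. It names a two-factor model, calls it balanced and fixes the reading of its interaction, for a comparison that is selected and not randomised.

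Second, the developmental safeguard is the control group's own change over an interval of matched length, and group × time removes stable differences. This is correct and limits the problem to factors that alter the rate of change. It does not remove it, since equal intervals give equal developmental change only if the rescanned groups would develop at similar rates. The intervals are also anchored differently: "approximately 24 weeks following their first therapy appointment" for patients, but for controls "All healthy comparison participants will be invited back for a second MRI visit at least 24 weeks from their first scan date". That is a separate point and is not counted in the sizes above.

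Third, *balanced* may mean only that each analysed person has both scans. That is possible, but the article does not say so.

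Some stronger readings are tempting and are not supported:
- That drop-out does break the matching. No data in the article link attendance or return to age, sex or IQ.
- That controls are matched to all 120 patients, and so not to the CBT arm. The article does not say to whom they are matched. Arms are randomly allocated, so the CBT arm has the same expected profile in any case.
- That the ±0.6 years is a bias. It is chance variation.

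**Conclusion.** The point holds as a risk that the stated model leaves open, not as a demonstrated failure. Matching is set at recruitment, the patient side is then filtered by a rule that controls do not face, and the model as written names no covariate and assumes a balance that 32 of 40 patients against up to 40 controls does not assure.

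The bias is modest: at most 0.08 SD at 20% loss and 0.16 SD at 40% loss, under assumed age gaps of up to 2 years and slopes of up to 0.2 SD per year. It is zero if either loss or 24-week change is unrelated to age. The type I figures apply to a single test, whereas the planned inference is nonparametric and corrected for multiple comparisons. Power is not affected in any way that matters. The change is worth making because it protects a safeguard the article relies on at almost no cost.

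**What to change.** In the Longitudinal data analysis plan:
- Drop *balanced*, or say how balance is restored in the rescanned set (for example by re-matching controls).
- Add baseline age × time and sex × time to the group × time model, with IQ × time as a sensitivity analysis. With two scans this amounts to regressing each person's change on group, age and sex. The planned nonparametric inference can accommodate it, for example by Freedman–Lane permutation.
- Tabulate age, sex and IQ for the rescanned CBT patients and the rescanned controls, beside the full baseline groups.

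No new data should be needed, since these variables must be obtained for matching. With 32 + 40 = 72 participants, the comparison of change has 72 − 2 = 70 residual degrees of freedom. Age and sex take two and IQ one more. Adjustment does not remove the other limit on calling the interaction a CBT effect: there is no untreated depressed group.
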